### Data collection

The effects of the intervention will be assessed by comparing key outcome indicators among children in the intervention and the control groups. Comparisons between groups will be performed by measuring the outcome indicators at baseline and endline (see definitions in the participant timeline section) in the intervention and the two control groups. The surveys will be administered to children and caregivers using a structured questionnaire. We will also conduct oral health and nutritional status assessments of the children in all groups and investigate the CD4 counts and registered clinical data of children living with HIV in groups A and B.

Six research assistants will receive a 1-day training session to ensure their understanding of the questionnaires. After the training, they will administer the questionnaires to 10 children as a pre-test. Two dentists and two dental assistants will receive a half-day training session for oral health data collection. After the training, they will collect oral health data from five children for a pre-test. The data collected for pre-test will not be included in the main analysis.

#### Questionnaires

Separate questionnaires will be developed for the children and caregivers. The questionnaire for children will be administered only to children aged 6–15 years and will solicit information regarding socio-demographic characteristics, HIV symptoms, oral health knowledge, attitudes and perceptions, and oral health-related/overall health-related quality of life. The questionnaire for caregivers will solicit information regarding soci-demographic characteristics, oral health knowledge, attitudes and perception, the child’s adherence to ART, and dietary diversity. The questionnaires will be developed based on existing tools adapted from previous studies [36–38]. To increase the validity of these tools, the questionnaires will first be developed in English and translated into Khmer. The accuracy of the translations and reliability of the contents will be reviewed by three native Khmer-speaking health specialists in the research team. Additionally, the questionnaires will be pre-tested, and inappropriate questions will be revised accordingly.

The quality of life will be measured both for overall health and oral health. Overall health-related quality of life will be measured using the Pediatric Quality of Life Inventory 4.0 (PedsQL ™ 4.0) [36]. This inventory is validated for HIV-infected children. The PedsQL ™ 4.0 is composed of 23 question items across four subscales: physical, emotional, social, and school functioning. The responses for each item are presented in the form of a 5-point response scale: ”never” = 0, ”almost never” = 1, ”sometimes” = 2, ”often” = 3, and ”almost always” = 4. Items will be reversed scored and linearly transformed to a 0–100 scale: 0 = 100, 1 = 75, 2 = 50, 4 = 0. The score is calculated based on the sum of all the items over the number of items answered on all the scales. The total score ranges from 0 to 100; a higher score indicates a better overall health-related quality of life. Cronbach’s alpha was 0.77.

Oral health-related quality of life will be measured using the Child Perceptions Questionnaire, which was validated in Cambodia [39, 40]. It consists of 16 question items across four subscales: oral symptoms, functional limitations, emotional well-being, and social well-being. The responses of each item are also presented in the form of a 5-point response scale: ”never” = 0, ”once or twice” = 1, ”sometimes” = 2, ”often” = 3, and ”every day or almost every day” = 4. The total score ranges from 0 to 64. A higher score indicates worse oral health-related quality of life. Cronbach’s alpha was 0.81.

#### Oral health status

The children’s oral health status will be assessed by examining the number of DMFT, the debris index, salivary pH, salivary flow, and number of cariogenic bacteria. The debris index will be calculated based on the degree of dental plaque. Dental plaque will be evaluated by colorizing the children’s teeth with a plaque test kit. The salivary pH will be assessed using CAT21Buf© (Morita, Osaka, Japan). The salivary flow will be measured as the total quantity of saliva produced in 3 min with stimulation from chewing gum. CariScreen© (CariFree, Albany, OR, USA) will be used to count cariogenic bacteria in saliva collected from the front teeth. All the oral health data will be collected by two dentists with the help of two dental assistants from the National Pediatric Hospital.

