### Interventions

Children and caregivers in group A will receive an intervention for 2 years (May 2018–April 2020). The main components of the intervention will comprise oral health education sessions and daily oral self-care. Prior to the intervention, two dental assistants from the National Pediatric Hospital will be appointed to receive a 1-day training course in conducting the oral health education sessions and intervention follow-up. Subsequently, these professionals will disseminate oral health education sessions to the children and caregivers under the supervision of the dentist every 4 months during the 2-year intervention period (in total six sessions for each participant). The initial education session will be provided with the contents presented in Table 1. The dental assistants will also provide the follow-up sessions to the initial session. Each 60-min session, including practice of the oral health procedure, will be attended by groups of 10 child-caregiver pairs. The education session will aim to teach the children and caregivers about correct brushing and the importance of daily oral care. Teaching tools will be developed based on publicly accessible basic oral health education materials which are used in Japan and the USA at school or dental clinics [33, 34].

**Table 1 Tab1:** Contents of oral health education session

Session 1: Knowledge	
1. What is tooth decay?	
2. Causes and prevention of tooth decay	
Session 2: Practice	
1. Brushing	
2. Flossing	
Session 3: Evaluation of oral health status	
1. Check plaque status using tester	
Session 4: Home-based daily oral care	
1. What one needs to do at home for daily care	
2. Follow-up schedule	

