### Outcome measures

The primary study outcome will be the change in oral health status, which will be measured according to the children’s individual DMFT. The secondary outcome will be the CD4 count. The other important outcomes include the salivary pH level, number of cariogenic bacteria, debris index score, salivary flow, nutrition status (height and weight), overall or oral health-related quality of life, and frequency of daily oral care. Details are presented in the data collection section and Fig. 2.

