### Randomization

After the baseline survey, the children living with HIV will be randomly allocated to an intervention group in a 1:1 ratio. A computerized algorithm will be used to generate a randomization scheme to assign participants to the study arms. The allocation will be implemented by a data analyst who is not a primary member of the study team. A member of the research team will inform the participants of their allocation. The research assistants, principal investigator, and primary study team members will be blinded to the group allocations until after the participants have completed the baseline assessment.

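### No masking is stated for the endline DMFT examination, and nothing separates the hospital dental staff who teach group A from those who score it

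*Protocol article*

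**What the plan says.** All references are to the Protocol article.

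- **Delivery.** Interventions states that "two dental assistants from the National Pediatric Hospital will be appointed to receive a 1-day training course in conducting the oral health education sessions"; the course covers follow-up as well. They then teach group A "under the supervision of the dentist every 4 months during the 2-year intervention period", six sessions per participant.
- **Measurement.** Data collection states: "Two dentists and two dental assistants will receive a half-day training session for oral health data collection". Oral health status then states: "All the oral health data will be collected by two dentists with the help of two dental assistants from the National Pediatric Hospital".
- **Outcome and timing.** Outcome measures states: "The primary study outcome will be the change in oral health status", measured by each child's DMFT. Data collection adds: "Comparisons between groups will be performed by measuring the outcome indicators at baseline and endline", in all three groups.
- **Masking.** Randomization contains the only blinding statement. It covers the research assistants and, in its own words, "principal investigator, and primary study team members will be blinded to the group allocations until after the participants have completed the baseline assessment". Dentists and dental assistants are not named.

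**The concern.** Children and caregivers cannot be blinded to an education programme, but examiners can. Masked examination is therefore the main protection available for an outcome that depends on judgement. Deciding whether a tooth is decayed involves clinical judgement, and so does grading plaque for the debris index.

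The plan does address masking, but its rule stops where masking would begin to matter for the treatment comparison. Teaching and measurement are both given to dental staff of one hospital, with the same numbers and job titles for the assistants. Followed as written, the plan allows the endline scores to be given or recorded by people who taught, or supervised the teaching of, the children in one arm. Any tendency to score those children more leniently would appear as an intervention effect on the primary outcome, and no analysis could remove it afterwards.

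**Working it through.** **Step 1. Set the sections side by side.**

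| Question | What the article fixes | Section |
|---|---|---|
| Who teaches group A? | Two dental assistants of the hospital | Interventions |
| Who supervises? | The dentist, not further identified | Interventions |
| Who collects DMFT and debris data? | Two dentists helped by two dental assistants of the same hospital | Data collection; Oral health status |
| When? | Baseline and endline | Data collection; Participant timeline |
| Who is blinded? | Research assistants, principal investigator, primary study team | Randomization |
| Until when? | Completion of the baseline assessment | Randomization |

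Randomization also says that allocation follows the baseline survey. During the period the rule covers, there is no allocation yet to know. For the endline examination it gives no protection to anyone, and dental staff are outside it throughout.

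Two further places point the same way. The education contents (Table 1) include a plaque check, so the teaching staff work with group A on the feature that underlies the debris index. Data management has research assistants collecting oral health data on the paper form. If they act as recorders, their blinding has ended and they have been reviewing group A's notebooks (Follow-up).

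**Step 2. Illustrate what a scoring shift would do.** The plan gives no figure for this, so there is nothing of its own to reproduce. Inputs:

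- SD 3.3 (Sample size). This is a cross-sectional SD at ages 8–15; no SD of change is given.
- Number per arm: 260 less 10% attrition = 260 × 0.9 = 234 (Sample size).
- Two-sided 5% test. The level is in Sample size; two-sided is assumed.
- Differential scoring shift b = 0.1, 0.2 or 0.3 teeth between groups A and B. **These are assumptions**; the article gives no basis for any value.
- No true effect.

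Standard error of the difference: SE = SD × √(2/n) = 3.3 × √(2/234) = 3.3 × 0.09245 = 0.305.

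False-positive rate = Φ(b/SE − 1.96) + Φ(−b/SE − 1.96).

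| Assumed shift b | Share of planned 0.7 | b/SE | False-positive rate, SD 3.3 | Same, SD of change 2.0 (assumed) |
|---|---|---|---|---|
| 0 | 0% | 0 | 5% | 5% |
| 0.1 | 14% | 0.33 | 6.2% | 8.4% |
| 0.2 | 29% | 0.66 | 10.0% | 19.1% |
| 0.3 | 43% | 0.98 | 16.6% | 36.8% |

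The last column uses SE = 2.0 × 0.09245 = 0.185. It shows the sensitivity to the missing SD of change.

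The planned 260 per group does not itself follow from a difference of 0.7 and SD 3.3: two-sided 5% and 80% power give 349 before attrition. That is a separate matter and does not affect this point. Here 234 is simply the number the plan expects to analyse per arm.

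**The case against.** **The staff may be different people.** A reader might infer that those who deliver the intervention also score its primary outcome. The article does not say so. It trains teachers and data collectors in separate courses, never states that the two pairs of assistants are the same, and never states that the supervising dentist is one of the two examiners. Dentists lead the data collection and assistants help. This objection stands: overlap is a reasonable inference from number, role and hospital, but it is not a stated fact. It does not remove the point, because no section excludes overlap or masks the examiners.

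**Examiners will know both arms.** One might also infer that they will have met group A repeatedly and group B never. That is not supported either. The dental staff collect oral data in every group at baseline, and group B are patients of a hospital with its own dental clinic, where they may seek care. The documented imbalance is in study sessions, which only group A attends.

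**The article may be silent rather than wrong.** The blinding rule does not name dental staff, and the SPIRIT checklist and figures are not shown. Details of masked examination could sit there. This has some weight. However, the article states a masking rule with an end point, and it states who teaches and who measures. What it fixes leaves endline open.

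**The size is hypothetical.** It is tempting to say that a small shift could create or double the effect. That compares the shift with the 0.17 teeth (0.99 − 0.82) seen in the cited school trial. This trial plans for 0.7, and shifts of 0.1 to 0.3 are a minority of that. At the low end the inflation is only from 5% to about 6%.

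**Conclusion.** The point holds as a gap in protection against detection bias. The article states no masking for the endline oral examination, and it gives both the teaching of group A and the collection of DMFT to dental staff of one hospital without separating the roles. It does not establish that the same individuals do both, or that any bias will occur; the direction and size of a shift are unknown.

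Under assumed shifts of 0.1 to 0.3 teeth, with SD 3.3 and 234 per arm, the false-positive rate would be about 6% to 17% instead of 5%. It would be higher if the SD of change is smaller than 3.3. The change should be made before endline, because unmasked scores cannot be repaired in the analysis.

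**What to change.** Amend Randomization and Oral health status so that masking extends to the endline oral examination, using existing staff:

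1. Call children from all three groups from one mixed list showing study ID only. They attend without notebooks and are asked not to mention the sessions.
2. Assign teaching and its supervision from the start, so that anyone who teaches or supervises group A neither scores nor records the endline oral examination **for any group**. Limiting the exclusion to groups A and B would require knowing the group at the chair and would defeat the ID-only list.
3. Draw any replacement recorder from existing staff and include that person in the half-day data-collection training. A research assistant who has reviewed group A's notebooks is best avoided.
4. Lock the tooth-level form before any intervention data are opened.

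**Cost.** Scheduling work, a slower endline survey if one dentist carries most examinations, and fewer examiners in common between baseline and endline, which matters for a change outcome. If full role separation is not feasible, apply at least the mixed ID-only list and the no-notebook rule, and report who examined whom.

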#### Nutrition status

To assess the children’s nutrition status, their body weight (in kilograms) and height (in centimeters) will be measured. Electronic scales and a stadiometer, which calibrate to 0.1 kg and 0.1 cm, respectively, will be used. Data will be collected by the nursing staff of the National Pediatric Hospital. The Z-scores of weight for age, height for age, and body mass index (BMI) for age will be calculated using the WHO tool AnthroPlus (available at http://www.who.int/growthref/tools/en/).

#### Clinical records

The clinical records of children living with HIV will be collected by research assistants from the registered documents of the National Pediatric Hospital. The following data will be recorded for the study purposes: CD4 count, history of opportunistic infections, ART regimen, and duration of ART use.

### Data management

The questionnaire responses and follow-up data will be entered directly into Open Data Kit 2.0 (ODK; available at https://opendatakit.org/use/2_0_tools/) by the research assistants. Oral health, weight, height, CD4 counts, and other registered clinical data will be collected by research assistants using a paper-based form. Supervisors will check the data collected during visits for accuracy and completion. Collected paper-based data will be entered electronically by the data management assistant. This will be done at the National Pediatric Hospital. Verification checks will be performed to correct discrepancies in the records. The original forms will be kept on file at the National Pediatric Hospital.

### Statistical analyses

Baseline and endline surveys will be conducted to assess changes in each outcome in both the intervention and control groups. To minimize overestimation of intervention impact, all intervention outcomes will be estimated with an intention-to-treat analysis. Initially, survey data will be stratified by different age groups: 3–5 years old, 6–11 years old, and 12–15 years old. Then, the data will be descriptively analyzed to assess the distributions of various factors related to the children and caregivers under the study. Next, bivariate analyses will be conducted to assess the correlations of each oral health indicator (DMFT, debris index, bacterial number, salivary pH, salivary flow, oral-health related quality of life) with different variables, using the chi-square test (or Fisher’s exact test when a count is smaller than five) for categorical variables, and Student’s *t* test for continuous variables. Then, we will apply a generalized estimating equation model [41] adjusted for basic demographic characteristics (e.g., sex) and factors identified as significantly associated with the outcome in the bivariate analyses. The statistical significance will be set at a *p* value < 0.05. All data analyses will be performed using IBM SPSS, version 24.0 (SPSS Inc., Chicago, IL, USA).

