### Study population and selection criteria

The study will comprise three groups: an intervention arm (group A) and two control arms (groups B and C) (see Fig. 1). The targets of groups A and B will be children living with HIV and their caregivers. Randomization will be performed for groups A and B using a 1:1 allocation protocol. The targets of group C will be HIV-uninfected children and their caregivers, comprising children age-matched with those in group A. Children eligible for groups A and B of the trial must meet all of the following inclusion criteria at randomization: (1) age 3–15 years, (2) have a patient ID at the National Pediatric Hospital, and (3) have received ART for at least 3 months. Children eligible for group C must be aged 3–15 years and must not have been diagnosed with HIV infection. For caregivers in all groups, individuals will be eligible if they are aged ≥ 18 years and self-report as the primary caregiver of the respective child.

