### Sample size

We calculated the sample size for the intervention and control groups as follows. We estimated that the intervention may suppress the increment of DMFT for around 17% based on the results of a previous study conducted in Cambodia among 8000 uninfected school children in five provinces. In that study, increments of DMFT of intervention and control groups were 0.82 and 0.99, respectively, after a 2-year intervention [35]. According to our situation analysis survey, which was conducted at the same study site in February 2017, for children living with HIV aged 8–15, the mean DMFT was 4.34 (standard deviation 3.3). We estimate that the intervention may suppress the increment of DMFT by 0.7 point, which equates to the 17% decrease in the mean DMFT. To detect this difference in our intervention group, at a power of 80% and a 5% significance level, 260 samples will be required for each group with a potential attrition of approximately 10%. In total, 780 pairs will be required for the three groups.

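### The primary DMFT question is set against two unranked comparators at one unadjusted 5% level, and the protocol never says that the randomised comparison, A versus B, decides it

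*Protocol article*

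**What the plan says.** - **Endpoint.** Outcome measures names one: "The primary study outcome will be the change in oral health status, which will be measured according to the children’s individual DMFT".
- **Comparators.** The first specific objective, at the end of the Background, sets the DMFT increment in the intervention group against untreated peers both with and without HIV. Data collection says "Comparisons between groups will be performed by measuring the outcome indicators at baseline and endline" and goes on to list the intervention group and both control groups, with no order of priority.
- **Standing of group C.** Study population and selection criteria says "Randomization will be performed for groups A and B using a 1:1 allocation protocol". Under Recruitment, group C is sampled from community lists. The Interventions section nevertheless describes B and C together as randomised controls.
- **Sample size.** It uses one SD ("the mean DMFT was 4.34 (standard deviation 3.3"), one difference ("We estimate that the intervention may suppress the increment of DMFT by 0.7 point, which equates to the 17% decrease in the mean DMFT") and one error rate ("at a power of 80% and a 5% significance level, 260 samples will be required for each group with a potential attrition of approximately 10" per cent). Group C gets the same 260.
- **Analysis.** Statistical analyses begins: "Initially, survey data will be stratified by different age groups: 3–5 years old, 6–11 years old, and 12–15 years old". Descriptive work follows, then bivariate tests, then a generalized estimating equation model. A single rule closes the section: "The statistical significance will be set at a *p* value < 0.05".

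**The concern.** Two contrasts answer one primary question, and they can disagree. Group A might do better than C but not better than B, or the reverse, and nothing in the protocol says which result answers whether the intervention works. The two are not of equal worth. Only A versus B is protected by randomisation. A versus C also compares children with and without HIV, and the Background itself says that children living with HIV tend to develop more caries.

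The answer has consequences. Post-trial care makes the offer of the intervention to the control groups depend on a positive impact that is not defined, and the Discussion would use a positive result to promote such programmes. If either contrast may carry that claim, the 5% level in the sample size section does not describe the chance of a false one. The unclear role of the age strata could widen the choice further.

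**Working it through.** **1. The plan's own figure.** Inputs from Sample size: difference 0.7, SD 3.3, alpha 5%, power 80%, attrition about 10%. Sidedness is not stated.

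n per group = 2(z₁₋α/₂ + z₀.₈₀)² × SD² / difference² = 2 × (1.960 + 0.842)² × 3.3² / 0.7² ≈ 349, or 349/0.9 ≈ 388 with attrition. One-sided gives 275 (306). Taking the difference as 17% of 4.34 = 0.738 gives 315 (350) two-sided and 248 (276) one-sided.

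None of these gives the stated 260. That is a separate matter. What counts here is that the calculation has one difference and one alpha, with no allowance for a second comparator.

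**2. Two comparators, all ages pooled.** Assume equal group sizes and variances, and no difference among A, B and C in mean change. The contrasts share A, so their correlation is (σ²/n) / (2σ²/n) = 0.5.

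- Either significant, two-sided: 1 − P(|Z₁| < 1.96 and |Z₂| < 1.96) = 0.0907, which is 0.0907/0.05 = 1.8 times the stated level. Independent tests would give 1 − 0.95² = 0.0975.
- Either significant in favour of A: 1 − P(Z₁ < 1.96 and Z₂ < 1.96) = 0.0454, against 0.025 for one test.
- Both significant: 0.05 + 0.05 − 0.0907 = 0.0093. A rule that requires both never exceeds 5%.

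**3. If the strata were tested as well.** The three age groups contain different children, so results are independent across strata.

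| Tests, any one sufficing | Two-sided | Favouring A only |
|---|---|---|
| A versus B, all ages | 5.0% | 2.5% |
| A versus B and A versus C, all ages | 9.1% | 4.5% |
| A versus B in three strata | 1 − 0.95³ = 14.3% | 1 − 0.975³ = 7.3% |
| Both contrasts in three strata | 1 − (1 − 0.0907)³ = 24.8% | 1 − (1 − 0.0454)³ = 13.0% |

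The Abstract counts permanent teeth. On the assumption that children aged 3–5 have too few for that stratum to contribute, the last row falls to 1 − (1 − 0.0907)² = 17.3% two-sided.

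**4. Which rows the text supports.** The second row follows from the two comparators in the objective, provided that either suffices. The third and fourth rows also need the group effect on DMFT to be tested in each stratum, which Statistical analyses neither states nor excludes. It goes from stratifying straight to description, and no later step says whether the data are pooled again.

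**The case against.** The strongest reply has five parts.

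- **Strata.** A reader might infer that the plan makes six DMFT tests and carries a false-positive rate near 25%. The text does not support that as fact. The step after stratification is descriptive, the model is mentioned in the singular, and nothing says that it is fitted per stratum or that one positive stratum counts as success. This part stands: 24.8% is a worst-case reading, not the plan's error rate.
- **Either or both.** The objective could mean that A must do better than both comparators, which keeps the error at or below 5%. The wording allows this, so the 9.1% is conditional. Leaving the reader to choose between the two readings is the defect.
- **Group C's null.** C is unrandomised and HIV-uninfected, so equal mean change is doubtful, and a significant A versus C may reflect HIV status rather than chance. This weakens 9.1% as a literal error rate. It also strengthens the case for keeping C out of the deciding test.
- **Cues to A versus B.** Only A and B are randomised, the Abstract introduces C as a second control, and the SD comes from children living with HIV. These cues are real but implicit, and the Interventions section undercuts them by calling C randomised too.
- **Condensed article.** Handling of multiplicity is often left to an analysis plan. That is fair for alpha allocation, and its absence alone is not raised here. The objective and its comparators are protocol content, however. An analysis plan that named only A versus B would narrow the objective as written, and one that kept both would need an allowance that the sample size does not make.

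**Conclusion.** The point holds in a limited form. The protocol sets its primary outcome against two unranked comparators, one of them not randomised, under a single unadjusted threshold, while the trial is sized for one comparison at 5%.

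The supportable size is about 9.1% two-sided against 5%, or 4.5% against 2.5% in the favourable direction. It rests on three assumptions: either contrast is enough for a claim, C shares the null mean change, and group sizes and variances are equal. The unclear role of the age strata could take the figure to about 25% (13% in the favourable direction), but only if both contrasts are tested in every stratum and any one success suffices. That should be reported as the upper end of a range. The point is worth correcting because an unrandomised contrast could otherwise carry the primary claim. It does not show that the trial is invalid.

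**What to change.** In the specific objectives, Data collection and Statistical analyses:

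- Name one primary test: A versus B, change in DMFT from baseline to 2 years, all randomised children in one model with age as a covariate, two-sided 5%.
- Label A versus C as secondary or descriptive, and correct the Interventions wording that presents C as randomised.
- State that the age-stratum results are subgroup estimates, reported with an age-by-arm interaction and no separate claims of effectiveness.

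This costs wording only, with no extra data or participants, and is most credible if settled before endline data are seen. The small downside is that a positive result against C alone, or in one stratum alone, can no longer be claimed as the trial's result.

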### Follow-up

After each 4 months follow-up education session by the dental assistants, children and caregivers in the intervention group will meet the research assistants for monitoring of the children’s daily oral self-care performance. The research assistants will note the number of seals placed in each child’s daily record notebook and the number of checks in the weekly checklist. Then, the children will be asked questions regarding their health status in accordance with the overall/oral health-related quality of life questionnaires, and their height and weight will be measured. Only the CD4 counts will be measured once a year.

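### The GEE named for DMFT does not clearly condition on baseline DMFT, so the A–B effect can be biased if loss differs by arm and relates to baseline DMFT; conditioning would remove this at almost no cost

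*Protocol article*

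**What the plan says.** - **Model** (Statistical analyses): "Then, we will apply a generalized estimating equation model [41] adjusted for basic demographic characteristics", and for factors that were significant in bivariate tests. No working correlation is given. Baseline DMFT is not named as a covariate. With data from two surveys it would most naturally enter as a response.
- **Population** (same section): "all intervention outcomes will be estimated with an intention-to-treat analysis".
- **Time points** (Participant timeline; Data collection): baseline and two years, in all groups.
- **Attrition** (Sample size): "260 samples will be required for each group with a potential attrition of approximately 10" per cent, not split by arm.
- **Contact between surveys** (Interventions; Follow-up): group A has education sessions every four months with supplies, and after them "children and caregivers in the intervention group will meet the research assistants for monitoring". No such contact is described for group B.
- **Order of events** (Randomization): allocation follows the baseline survey, so baseline DMFT should exist for every randomised child.

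**The concern.** The intention-to-treat label keeps each child in the allocated arm. It does not recover an endline that was never measured, and an unweighted GEE recovers it only as far as its working correlation borrows from the baseline record. The children most likely to be lost may differ in baseline DMFT from those retained. If they are also lost at different rates in A and B, the endline means of the two arms come from differently selected children.

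The result could go either way. If group B loses more children with high DMFT, the intervention looks worse than it is. If the lost children have low DMFT, or group A loses more, the error is reversed. Baseline DMFT, which would correct for this, will already be in hand. A weak working correlation also costs precision when loss is equal and random.

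**Working it through.** **Inputs from the protocol (Sample size).** 260 per arm; about 10% attrition, so 260 × 0.9 = 234 completers; DMFT mean 4.34, SD 3.3 (variance 10.89); control increment 0.99; cited earlier difference 0.99 − 0.82 = 0.17; planned effect 0.7.

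**The plan's own figure.** With delta 0.7, SD 3.3, two-sided 5% and 80% power, n = 2 × (1.96 + 0.84)² × 3.3² / 0.7², about 349 per arm, or 388 after dividing by 0.9. So 260 is not reproduced. That is a separate matter, and nothing below depends on it.

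**Assumed, not in the protocol.** Increment independent of baseline, with variance 0.99 + 0.99² = 1.97, so endline variance is 10.89 + 1.97 = 12.86; loss of 8% in A and 12% in B, or 5% and 15%; lost children 0.6 to 1.2 SD higher at baseline, a gap D of 0.6 × 3.3 = 1.98 to 1.2 × 3.3 = 3.96 teeth.

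**Step 1: bias formula.** In an arm that loses a fraction d, the retained children's baseline mean is below the arm's mean by d × D. Let β be the true slope of endline on baseline and ρ the working correlation. The GEE corrects the endline mean by ρ × d × D where β × d × D is needed. Hence

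bias(A − B) = (β − ρ) × (d_B × D_B − d_A × D_A).

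If loss depends on arm alone, D = 0 and the bias is zero. If the analysis conditions on baseline, ρ is replaced by the fitted β and the bias is zero.

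**Step 2: independence (ρ = 0, β = 1, equal gaps).**
- 8/12%: 0.04 × 1.98 = 0.08, up to 0.04 × 3.96 = 0.16.
- 5/15%: 0.10 × 1.98 = 0.20, up to 0.10 × 3.96 = 0.40.

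Simulation under no effect (3,000 runs, skewed counts, logistic loss on baseline DMFT) gives somewhat less, because the same dependence on baseline produces a smaller gap in the arm with more loss:

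| Loss A/B | Independence | Exchangeable | Conditioned on baseline |
|---|---|---|---|
| 8/12% | 0.072 to 0.124 | 0.006 to 0.014 | about 0 |
| 5/15% | 0.177 to 0.309 | 0.013 to 0.029 | about 0 |

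Separately coded versions gave up to 0.33 for independence and up to 0.07 for exchangeable.

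**Step 3: why exchangeable helps but is not exact.** The full-data correlation is √(10.89/12.86) = 0.92, so β − ρ = 0.08 and about 8% of the independence bias remains. Selective loss lowers the estimated ρ, so somewhat more remains in practice.

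**Step 4: precision with equal, random 10% loss.** Variance of the A–B change:
- independence GEE: 2 × (12.86/234 + 10.89/260 − 2 × 10.89/260) = 0.0261, SE 0.162;
- conditioned on baseline: 2 × 1.97/234 = 0.0168, SE 0.130.

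The ratio is 1.55.

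**Step 5: a harsher case.** True effect −0.70; about 5% random loss in A; about 16% loss in B that depends on baseline DMFT; increments that rise with baseline (β = 1.3). Independence gives −0.24, exchangeable −0.54 and completer ANCOVA −0.70. If loss in B depends on endline DMFT instead, the three give −0.17, −0.45 and −0.59, so conditioning leaves 0.11 of bias.

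**The case against.** The strongest reply is that this is missing-data detail, which a journal article may leave to an analysis plan that is not shown. A weighted GEE, or a GEE after imputation, would still be the stated GEE. That stands as far as it goes: the lack of a missing-data section is not the point here. The point is the choice of a named model that does not clearly use baseline DMFT as a conditioning variable.

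Several stronger readings are tempting, and the protocol does not support them:

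- **That missing endlines are dropped.** The protocol does not say so. It is how an unweighted GEE behaves, and the lost child's baseline record still contributes.
- **That the GEE is valid only if data are missing completely at random.** This is too strict. With 5% against about 14 to 16% loss depending on arm alone, or on arm and a modelled covariate (age), simulation returned −0.70 for a true −0.70.
- **That group B goes unseen for two years and will lose more children.** Neither is documented. A and B come from the same hospital, described as the only provider of pediatric ART in Phnom Penh, and clinical records are collected for both. The timeline figure is not shown.

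It is also fair that all loss rates and gaps are assumed, that exchangeable correlation removes most of the bias in the main scenarios, and that the planned effect is 0.7 rather than 0.17. On the assumed variances the precision loss would not endanger detection of 0.7: the largest simulated SE, 0.199, is 0.7/3.5.

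**Conclusion.** The point holds as a conditional risk in the named model, not as a demonstrated error. Two conditions are needed together: loss that differs by arm, and loss that is related to baseline DMFT beyond the modelled covariates. Under the assumed main scenarios the bias is roughly 0.1 to 0.3 DMFT with independence (0.1/0.7 = 14% to 0.3/0.7 = 43% of the planned effect) and about 0.01 to 0.07 with exchangeable (1% to 10%). Against the cited earlier difference of 0.17, the independence figures are of the same order as the effect. The protocol fixes neither correlation, so it does not say which range applies. The precision cost with independence, about 1.5 times the variance, needs no unequal loss but does rest on the assumed increment variance of 1.97.

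A reader might infer that the intention-to-treat statement is false or the A–B result invalid. Neither follows. This is a low-cost improvement that makes the estimate robust to one foreseeable kind of loss.

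**What to change.** Estimate the A–B effect on DMFT conditioning on baseline DMFT, in one of two ways:

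1. endline DMFT adjusted for baseline DMFT; or
2. a two-time-point model of all baseline and endline values, with unstructured covariance and a baseline mean common to A and B, which randomisation justifies. Group C is not randomised and should not share that constraint.

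If the GEE is kept, use an exchangeable working correlation and multiply impute missing endline DMFT within arm from baseline DMFT, age and sex. In all cases, report attrition by arm and by baseline DMFT.

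The cost is a change of analysis wording and, if imputation is used, a little more analysis work. No new data are needed. The change does not remove bias from loss that depends on the unseen endline DMFT.
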